
#### Control arm

The patients in the primary care clinics assigned to the comparator will receive the usual treatment for depression and their physical conditions –all the guaranteed interventions for people with depression, hypertension, and/or diabetes in primary care, according to the Clinical Guidelines for the Treatment of Depression– and their associated basket of health benefits included in the Regime of Explicit Health Care Guarantees [34, 35].

In the specific case of depression, in Chile, this pathology is managed using a stepped care model, with more severe cases being addressed with more intense and frequent interventions [34]. The severity of depression is determined with the diagnostic criteria of the International Classification of Diseases, tenth version (ICD-10), which characterizes mild, moderate, and severe levels depending on the number of symptoms [34]. Mild cases are treated with low-intensity interventions such as counseling, support groups, and physical exercise programs; moderate cases are complementarily treated with antidepressants, depending on patients’ response and tolerance; finally, the treatment of severe cases also includes psychotherapy [34]. Depression cases with high suicide risk or psychotic symptoms, or which are refractory to treatment, are referred to psychiatric assessment or to specialized mental health services [34].

#### Criteria for discontinuing or modifying allocated interventions

Primary care team will be informed If patients assigned to the intervention or to the comparator present high suicide risk or a worsening of their depression during the trial.

Interventions will also be interrupted if a patient is hospitalized as a result of a worsening of his/her physical issues.

#### Strategies to improve adherence to interventions

Adherence to trial protocols will be ensured by training and supervising the therapists taking part in the trial. In addition, the therapists and the social worker will be asked to keep a record of each session with the patients, which will be reviewed by a psychiatrist from the research team to ensure adherence to the protocols. Lastly, 10% of the participants will be contacted by a blinded evaluator who will administer an ad-hoc questionnaire designed to assess the therapists’ fidelity to the intervention.

#### Relevant concomitant care permitted or prohibited during the trial

In those primary care clinics assigned to the intervention, usual psychological treatment will be replaced by the psycho-educational intervention.

#### Provisions for post-trial care

The risks associated with the intervention are minimal; therefore, this clinical trial does not entail a compensation for the participants. In addition, health care staff will receive training and materials associated with the intervention in all the participating primary care clinics at the end of the trial follow-up period.

## Outcomes

### Primary outcome

#### Depression improvement

Defined as a 50% reduction in a participant’s Patient Health Questionnaire-9 Item (PHQ-9) score compared to the baseline [36]. The summary measure for each group will be the percentage of participants who respond to their depression treatment at 6-month follow-up. Even though the primary outcome is taken at 6-month follow-up, this measure will also be reported at 3- and 12-month follow-up.

### Secondary outcomes

#### Depression recovery

Defined as a change in a patient’s depressive status from an initial score above the cutoff (PHQ-9 ≥ 10) and a follow-up score below this reference value (PHQ-9 < 10). The summary measure for each group will be the percentage of participants who respond to their depression treatment at 3-, 6-, and 12-month follow-up.

#### Health-related quality of life

Defined as a patient’s score on the scales and main components of the Short-Form 12 Health Survey (SF-12) [37]. The summary measure for each group will be the mean score of the participants at 3-, +-, and 12-month follow-up.

#### Social solving problem skills

Defined as a patient’s score on the Positive Problem Orientation and Rational Problem Solving Style subscales of the Social Problem-Solving Inventory – Revised Short Form (SPSI-R:S) [38]. The summary measure for each group will be the mean score of the participants at 3-, 6-, and 12-month follow-up.

#### Blood pressure and glycosylated hemoglobin

Defined as the achievement of therapeutic goals in the normalization of blood pressure and glycemic control, according to the national standards established in the Clinical Guidelines of Primary or Essential Arterial Hypertension in people aged 15 or older and in the Clinical Guidelines for Type II Diabetes Mellitus, respectively. With respect to arterial pressure, the therapeutic goal is to attain a value lower than 140/90 mmHg in non-diabetic patients and lower than 130/80 mmHg in patients with very high cardiovascular risk, diabetes, and/or proteinuric nephropathy. Maintaining levels of glycosylated hemoglobin below 7% is regarded as a therapeutic goal in type II diabetes mellitus. The summary measure for each group will be the percentage of participants who achieve these blood pressure and glycemic control goals at 3-, 6-, and 12-month follow-up.

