### Specific objectives

To compare the proportion of patients with improvement in depressive symptoms treated with the “Me cuido y me siento mejor” intervention versus enhanced usual care in primary care clinics.To compare the proportion of patients recovered from depression treated with the “Me cuido y me siento mejor” intervention versus enhanced usual care in primary care clinics.To compare the levels of health-related quality of life and social problem-solving skills in patients treated with the “Me cuido y me siento mejor” intervention versus enhanced usual care in primary care clinics.To compare the values of blood pressure and/or glycosylated hemoglobin of patients treated with the “Me cuido y me siento mejor” intervention versus enhanced usual care in primary care clinics.To compare treatment acceptability of the “Me cuido y me siento mejor” intervention versus enhanced usual care in primary care clinics.

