### Hypotheses

The proportion of patients with improvement in depressive symptoms will be 23% higher in the “Me cuido y me siento mejor” primary care clinics compared to the enhanced usual care primary care clinics, at 6-month follow-up.The proportion of patients recovered from depression would be higher in the “Me cuido y me siento mejor” compared to the enhanced usual care primary care clinics, at 6-month follow-up.Patients in the “Me cuido y me siento mejor” primary care clinics would have better social problem-solving skills and health-related quality of life than patients in the enhanced usual care primary care clinics, at 6-month follow-up.Patients in the “Me cuido y me siento mejor” primary care clinics would have lower blood pressure and improved glucose regulation than patients in the enhanced usual care primary care clinics, at 6-month follow-up.Patients in the “Me cuido y me siento mejor” primary care clinics would report higher treatment acceptability than patients in the enhanced usual care primary care clinics, at 6-month follow-up.

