#### Trial participants

*Inclusion criteria:*
Age 18 or older.Enrolled in the Cardiovascular Health Program (i.e. currently receiving treatment for diabetes and/or hypertension) at the study primary care clinics.Patient Health Questionnaire-9 Item (PHQ-9) score ≥ 15.Signed or verbal informed consent.

*Exclusion criteria:*
Functional illiteracy (i.e., patients unable to read and comprehend written information, such as the study questionnaires or written/verbal informed consent).Significant visual and/or auditive impairments (i.e., such as those imposing a serious difficulty to respond the study questionnaires or written/verbal informed consent).Pregnancy or breastfeeding.Cognitive impairment – ineligible patients would give a negative answer to questions “What year is it?” and “Where are we (place/address)?”.In treatment for bipolar and/or psychotic disorder.Current psychological treatment for depression.High risk of developing alcohol/substance abuse problems, according to an Alcohol, Smoking and Substance Involvement Screening Test (ASSIST) score ≥ 27 [33].

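### The objective compares blood pressure and HbA1c values, but the only outcome defined is the percentage at guideline goal, so no planned result compares values

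*Protocol article*

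**What the plan says.** Specific objectives, fourth item: "To compare the values of blood pressure and/or glycosylated hemoglobin of patients treated with" the intervention or enhanced usual care.

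Hypotheses, fourth item: patients in the intervention clinics "would have lower blood pressure and improved glucose regulation than patients in the enhanced usual care primary care clinics", at 6 months.

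Secondary outcomes, Blood pressure and glycosylated hemoglobin: "Defined as the achievement of therapeutic goals in the normalization of blood pressure and glycemic control". The blood pressure goal is "lower than 140/90 mmHg in non-diabetic patients and lower than 130/80 mmHg in patients with very high cardiovascular risk, diabetes, and/or proteinuric nephropathy". The HbA1c goal, below 7%, is given for type II diabetes. At 3, 6 and 12 months, "The summary measure for each group will be the percentage of participants who achieve these blood pressure and glycemic control goals".

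The statistical methods section sends dichotomous outcomes to random effects logistic regression with odds ratios. Continuous outcomes go to linear random effects regression with mean differences and Cohen's d.

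The section on assessment and collection of outcomes has blinded evaluators take blood pressure and HbA1c retrospectively from clinical records. Participants are "currently receiving treatment for diabetes and/or hypertension", so some may have only one of the two conditions.

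**The concern.** The objective and the blood pressure hypothesis ask about levels, while the outcome asks how many patients are under a line. These are different quantities and lead to different models. A non-diabetic patient whose pressure falls a long way but stays above 140/90 contributes nothing to goal attainment, and one who moves just across the line counts in full. The percentage at goal can therefore change, or fail to change, without answering whether values differ.

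The Discussion says that improvement in these physical indicators will be tested in this trial. As the plan stands, that test would rest on a different quantity from the one in the objective, and on a less informative one, although the numeric values have to be read from the records to judge goal attainment.

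**Working it through.** **1. Objective, hypothesis, outcome and analysis side by side**

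| Place | Blood pressure | HbA1c |
|---|---|---|
| Specific objectives | values | values |
| Hypotheses | lower (a level) | improved regulation (no scale named) |
| Outcome definition | at goal or not | at goal or not |
| Summary measure | percentage | percentage |
| Resulting model | logistic, odds ratio | logistic, odds ratio |

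The outcome section names no mean for either measure, although the sections on quality of life, problem-solving skills and acceptability each name a mean score. The mismatch is firm for the objective (both measures) and for the blood pressure part of the hypothesis. It is not firm for glucose regulation, which a percentage below 7% can test.

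**2. The plan's own figures**

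The Sample size section gives 4 clusters per arm, 38 participants per cluster and an ICC of 0.02.
- Design effect = 1 + (38 − 1) × 0.02 = 1.74, as stated.
- Detectable difference from 27% at 80% power: 20.0 points by the normal approximation with 4 clusters per arm, and 23.1 points if one cluster per arm is deducted for the small number of clusters. The second matches the stated 23.
- Recruitment: 38 / 0.85 = 44.7, rounded up to 45; 45 × 8 = 360, as stated.

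These figures concern PHQ-9 response. None is given for blood pressure or HbA1c, so what follows is illustration.

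**3. Information kept when a normal variable is dichotomised**

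Efficiency = φ(z_p)² / [p(1 − p)], where p is the share at goal, z_p the matching normal quantile and φ the normal density.

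| Share at goal | Efficiency |
|---|---|
| 50% | 0.637 |
| 40% | 0.622 |
| 30% | 0.576 |
| 20% | 0.490 |

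The maximum is 2/π = 0.637, at 50%.

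**4. The same loss as power**

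Effective n per arm = 4 × 38 / 1.74 = 87.4, with alpha 0.05 two-sided. For means, power = Φ(δ√(n/2) − 1.96). With δ = 0.35: 0.35 × √43.7 = 2.31; 2.31 − 1.96 = 0.35; Φ = 0.64. For goal attainment, the control share p is compared with Φ(z_p + δ) by the usual two-proportion formula.

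| Shift δ (SD, assumed) | Means | 50% of controls at goal | 30% of controls at goal |
|---|---|---|---|
| 0.25 | 38% | 26% | 25% |
| 0.35 | 64% | 45% | 43% |
| 0.45 | 84% | 65% | 64% |

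The table applies the depression outcome's design effect to both scales and assumes a recorded value for all 38 participants per cluster. It uses a normal reference, which is generous with 8 clusters. HbA1c would have fewer participants, so both of its powers would be lower.

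**The case against.** The strongest reply is that goal attainment is a deliberate and sound choice. The goals are guideline targets, the outcome is secondary and carries no power claim, and individual targets (140/90 or 130/80) are handled in a way that a single mean is not. Rewording the objective and hypothesis would then remove the conflict. Most of this stands: the loss of information is a cost of a legitimate choice and not in itself an error, and goal attainment should be kept. But rewording alone would give up a question that the trial set itself and can answer from the same records.

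Three stronger readings are tempting, and the text does not support them.

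- *Hypertension-only patients are counted in the HbA1c percentage.* The outcome section does not say that all participants form the denominator, and it ties the HbA1c goal to type II diabetes, so a diabetes-only denominator is a natural reading. The general intention-to-treat statement makes the other reading possible but does not state it. Dilution could be large if it were applied. Suppose 30 to 70% have diabetes and 40% against 55% of them reach goal (assumptions): 15 points would shrink to 4.5 to 10.5. This is a reason to state the denominator and not evidence of an error.
- *The whole hypothesis goes untested.* Glucose regulation can be tested with a 7% threshold.
- *Baseline status is excluded.* The section on additional analyses plans adjustment for sex, age and covariates reflecting imbalance. Baseline control is not named, but it is not ruled out. Nor is counting patients already at goal a mistake, since the HbA1c goal is worded as keeping levels below 7%.

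**Conclusion.** The concern holds as an inconsistency between the fourth objective, the blood pressure part of the fourth hypothesis and the outcome definition. Followed as written, the plan reports odds ratios for goal attainment and no comparison of values. An analysis plan would inherit this conflict, because the two texts lead to different models and effect measures.

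The loss of information is secondary to that. At most about 64% is kept under normality, which for an assumed 0.35 SD shift means roughly 20 points of power (64% against 43 to 45%). The documents give no standard deviations, goal rates or share with diabetes, so these figures show the order of the loss and do not predict this trial's power. The primary outcome and its sample size are unaffected. The point should be corrected, at modest cost.

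**What to change.** In the outcome section on blood pressure and glycosylated hemoglobin:

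- Add mean systolic and mean diastolic pressure, and mean HbA1c, at 3, 6 and 12 months, with 6 months as the time point for the fourth hypothesis. Take HbA1c in participants with diabetes, where its goal is defined.
- Analyse these with the linear random effects model already planned, adjusted for the baseline record value.
- Keep goal attainment as the accompanying outcome, also adjusted for baseline value or status. Calculate the HbA1c percentage among participants with diabetes. Assess blood pressure in every participant for whom the section gives a goal; restricting it to hypertensive patients would drop diabetic patients for whom a goal is set.
- Report the number of participants with a recorded value, by arm and measure.

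The therapeutic goals stay as they are. The cost is protocol wording, slightly more analysis, and extraction of baseline values from the same clinical records, which the data collection section does not currently mention.

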#### Acceptability of depression treatment

Defined as the score on an ad-hoc instrument for measuring the acceptability of depression treatment. The summary measure for each group will be the mean score of the participants at 3-, 6-, and 12-month follow-up.

### Other measures

Complementarily, we will evaluate the participants’ utilization of health care services and treatment adherence at 3-, 6-, and 12-month follow-up.

### Participant timeline

The participants’ timeline is shown in Fig. 1.

**Fig. 1 Fig1:**
[figure not shown]
Participant timeline

### Sample size

The meta-analysis conducted by Huang et al. [39], about the effectiveness of collaborative care in diabetic and depressed patients treated in primary health care showed that 27% of patients in the usual group responded to depression treatment. Considering a two-tailed alpha of 0.05, a statistical power of 80%, 4 clusters per treatment group, 38 participants per cluster, and assuming an intraclass correlation coefficient (ICC) of 0.02 –a more conservative ICC than that reported by Adams et al.– [40] with a design effect of 1.74, we calculated a minimum detectable difference of 23% between the treatment groups, with the expectation that 50% of the members of the active group will respond to depression treatment. Anticipating 15% attrition at follow-up, this study will need to recruit 45 participants in each of the 8 clusters (360 cases in total).

### Recruitment

A trained recruiter will be allocated to each of the primary care clinics taking part in the trial. Recruiters will contact potential participants in-person – at the primary care clinics’ waiting rooms – or remotely (e.g., via telephone call and based on lists of registered cardiovascular patients at the primary care clinics), if in-person contacts are not possible. Recruiters will inform patients of the study, evaluating the initial eligibility criteria and administering the informed consent. After securing the patients’ written informed – or verbal, if in-person contact is not possible –, and if they meet the initial eligibility criteria (e.g. PHQ-9 ≥ 15), potential participants will be contacted again by the recruiters for an in-person (or remote – e.g., telephone call) assessment 1 week later. During this period, recruiters will send reminders to potential participants using the available means of contact. In the reassessment, those with a PHQ-9 ≥ 15 will be recruited for the trial and will be invited to continue by answering the baseline evaluation.

To ensure a sufficient recruitment flow, recruiters will work every day of the week in the morning, when most people attend health care centers. These activities will be supervised by a person in charge of recruitment, who will be in close contact with members of the research team in charge of fieldwork. To facilitate the work of the recruiters, signs, leaflets, and banners with basic information about the study will be on display, inviting potential participants to contact the recruiters. Each recruiter will remain in the allocated primary care clinic until he/she has recruited 45 participants. Additionally, if in-person recruitment is not possible, the lists of registered cardiovascular patients at the primary care clinics will be obtained for the remote contact of potential participants.

### Assignment of interventions: allocation

#### Sequence generation

In each municipality, the four participating primary care clinics will be allocated to the intervention or the comparator with a 1:1 ratio based on random computer-generated numbers, using simple random sampling. This sampling method was used instead of others (e.g. stratified) because health care centers in each municipality tend to operate homogeneously and serve population with similar characteristics.

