**Methods:**

Two-arm, single-blind, CRT carried out at two municipalities in Santiago, Chile. Eight PCC will be randomly assigned (1:1 ratio within each municipality, 4 PCC in each municipality) to the INTERVENTION or EUC. A total of 360 depressed patients, aged at least 18 years, with Patient Health Questionnaire-9 Item [PHQ-9] scores ≥15, and enrolled in the Cardiovascular Health Program at the participating PCC. Patients with alcohol/substance abuse; current treatment for depression, bipolar disorder, or psychosis; illiteracy; severe impairment; and resident in long-term care facilities, will be excluded. Patients in both arms will be invited to use the Web page of the project, which includes basic health education information. Patients in the INTERVENTION will receive eight sessions of a computer-assisted, psycho-educational intervention delivered by trained therapists, a structured telephone calls to monitor progress, and usual medical care for chronic diseases. Therapists will receive biweekly and monthly supervision by psychologist and psychiatrist, respectively. A monthly meeting will be held between the PCC team and a member of the research team to ensure continuity of care. Patients in EUC will receive depression treatment according to clinical guidelines and usual medical care for chronic diseases. Outcome assessments will be conducted at 3, 6, and 12 months after enrollment. The primary outcome will be depression improvement at 6 months, defined as ≥50% reduction in baseline PHQ-9 scores. Intention-to-treat analyses will be performed.

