### Statistical methods

#### Statistical methods for primary and secondary outcomes

Results will be reported according to the Consolidated Standards for Reporting Trials (CONSORT), specifically its extensions for cluster randomized clinical trials and clinical trials of non-pharmacological interventions [47, 48]. We will check the balance between the baseline characteristics of the intervention groups. As a general rule, for dichotomous or categorical variables, we will present the percentage and frequency of each category of interest (e.g. response vs. no response to treatment) for each intervention group, along with the odds ratio (OR) as a measure of the effect, a 95% confidence interval (95% CI), and *p* value. For continuous variables, we will present the means and standard deviations for each intervention group, along with the mean difference between the groups, 95% CI, and *p* value. For the analysis of dichotomous outcomes (including the main outcome), we will fit logistic random effects regression models to reflect the grouped nature of the data and will report OR, with their respective 95% CI, as effect size measures. The same strategy will be used for continuous outcomes (i.e. difference in means between the groups) with linear random effects regression models and Cohen’s *d* (i.e. standardized mean difference), with their respective 95% CI, as effect size measure. These analyses will be assisted using Stata 14.0 [49].

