#### Methods for additional analyses (e.g. subgroup analyses)

Regarding the evaluation of the effects of the intervention (i.e. analysis of the main and secondary outcomes), raw and adjusted effect estimates will be presented. The adjustment will involve sociodemographic variables with a well-known diagnostic value (i.e. sex and age), complemented with covariables to reflect the potential imbalance between the intervention groups.

Additional analyses will consider the fit of repeated measures mixed effects models to determine whether the effect of the intervention differs over time, taking into account the correlation between the measures of a single participant, as well as the study design. The potential moderating effects of sex and age will be considered in these analyses.

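### Clinics are randomised 1:1 within each municipality, but the allocation is not called stratified and no model carries a municipality term, which loses power if the municipalities differ

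*Protocol article*

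**What the plan says.** The Abstract (Methods) fixes the allocation: "Eight PCC will be randomly assigned (1:1 ratio within each municipality, 4 PCC in each municipality) to the INTERVENTION or EUC". Sequence generation repeats it: "In each municipality, the four participating primary care clinics will be allocated to the intervention or the comparator with a 1:1 ratio". The same paragraph names the method simple random sampling and explains the choice: "This sampling method was used instead of others (e.g. stratified) because health care centers in each municipality tend to operate homogeneously".

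For the main analysis, the section on statistical methods for primary and secondary outcomes says "we will fit logistic random effects regression models to reflect the grouped nature of the data", with linear counterparts for continuous outcomes. The section on additional analyses promises raw and adjusted estimates: "The adjustment will involve sociodemographic variables with a well-known diagnostic value (i.e. sex and age". Beyond those two variables, others enter by a rule based on how the arms compare: "complemented with covariables to reflect the potential imbalance between the intervention groups". For the repeated-measures models it adds "taking into account the correlation between the measures of a single participant, as well as the study design". Municipality is named in none of these models.

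**The concern.** Fixing two clinics per arm in each municipality takes any municipality difference out of the treatment contrast. An analysis that ignores municipality does not take it out of the error term. The estimate then varies less between possible allocations than its standard error claims.

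The covariate rule would not repair this. It adds variables that turn out imbalanced, and municipality is balanced 2:2 by design. The phrase about the study design belongs to the additional repeated-measures models, not to the primary analysis.

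With eight clinics and a sample size set for 80% power, there is little reserve to absorb an inflated standard error. The wording also matters by itself: a reader who takes the stratification sentence at face value would see no reason to include the term.

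**Working it through.** **The plan's own figures.** Design effect: 1 + (38 − 1) × 0.02 = 1.74, as stated. Clusters per arm, with one added for the small number of clusters: 1 + 66.3 × 1.74 / 38 = 4.04, against 4 stated, where 66.3 = (1.96 + 0.84)² × (0.27 × 0.73 + 0.50 × 0.50) / 0.23². Solving the same form for the difference gives 23.2 points, against 23 stated. Recruitment: 38 / 0.85 = 44.7, rounded up to 45; 45 × 8 = 360. The calculation reproduces and has no municipality component.

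**The design.** An unrestricted draw of 4 clinics from 8 has 70 possible results. Drawing 2 of 4 in each of two municipalities has 6 × 6 = 36. The procedure described is the second one.

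**Effect on the standard error.** Inputs from the Sample size section: 38 per clinic, ICC 0.02, 27% and 50%. Assumption: a gap of D between the municipalities' response rates, taken from 0 to 20 points, with ICC 0.02 holding within municipality.

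- Average variance of a clinic's proportion: σ² = [(0.1971 + 0.25) / 2] × 1.74 / 38 = 0.01024.
- True standard error of the arm difference, four clinics per arm: √(σ² / 2) = 0.0715.
- Without municipality, each arm has two clinics at −D/2 and two at +D/2. This adds (4 × D²/4) / 3 = D²/3 to the estimated clinic variance, so the reported standard error is √[(σ² + D²/3) / 2].
- At D = 0.10: √[(0.01024 + 0.00333) / 2] = 0.0824, or 15% too large. At D = 0.05: 0.0744, or 4% too large.

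**Type I error and power.** These come from 200,000 simulated trials per scenario (beta-binomial), tested at clinic level with t on 6 df without municipality and t on 5 df with it.

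| Assumed gap (points) | Type I error without | Type I error with | Power without | Power with |
|---|---|---|---|---|
| 0 | 5.0% | 5.1% | 75.5% | 72.3% |
| 5 | 4.4% | 5.1% | 73.1% | 72.5% |
| 10 | 2.7% | 5.0% | 65.6% | 72.8% |
| 15 | 1.3% | 5.0% | 54.1% | 73.7% |
| 20 | 0.4% | 4.9% | 39.7% | 74.1% |

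Repeat runs at 10 points gave type I errors of 2.6% to 2.8% and powers of 65% to 66% without the term and 73% with it.

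**Wald z version.** With clinic variance floored at zero, as a rough stand-in for the planned random effects model, power without the term falls from 86.6% at no gap to 80.5% at 10 points, against about 86.6% with the term at 10 points. This test has its own fault: with the term, type I error is about 7.5% at every gap. Without the term it is 7.3% at no gap and 4.9% at 10 points, where the two faults roughly cancel. The municipality term therefore needs a small-sample reference distribution beside it.

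**The case against.** **The wording can be read consistently.** The allocation paragraph starts from each municipality, and its reason concerns likeness of clinics inside a municipality. That reason fits best if the sentence means that no further stratification was used there. On that reading, Sequence generation agrees with the Abstract. A reader might infer that the protocol contradicts itself about how clinics were allocated; the text does not force this, because the procedure is stated openly and identically in both places. What stands is that the name given to the procedure does not say what it is.

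**The term may be in a document not shown.** This is a condensed article, and a list of design terms is often left to the analysis plan. That would settle the model if so. But the article states its covariate rule, and that rule would leave municipality out, so this is more than missing detail.

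**The gap is assumed, and a large one strains the planned ICC.** Both municipalities are described as low-to-middle income and urban. A 10-point gap adds about (0.10² / 4) / 0.1971 = 0.013 to an ICC planned at 0.02. If 0.02 is meant as the total, municipality variation is already counted in the sample size. Holding the total at 0.02, a clinic-level test at a 10-point gap has power of about 74% without the term and 82% with it, and type I error of 2.3% without it. Omission then forgoes a gain and costs almost none of the planned power. At 5 points the two analyses are about equal. This limits the size of the point, but the overstated standard error remains.

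**Two further inferences are not supported.** A reader might infer that a positive result would be unsafe. Omitting the term makes the standard error too large, so it works against a positive finding. A reader might also infer a definite, large power loss in the planned model. The documents give no municipality gap and state no reference distribution for that model, so no such figure can be fixed.

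**Conclusion.** The point holds in limited form. The allocation is stratified by municipality, its label does not say so, and the stated models leave municipality out. The direction is certain: any municipality difference inflates the standard error, which costs power and does not create false positives.

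The size is conditional. In a clinic-level test with ICC 0.02 within municipality, omission is negligible at a gap of 5 points or less. At 10 points it costs about 7 points of power (66% against 73%), and type I error is about half its nominal level. If the municipalities do not differ, nothing is misstated and leaving the term out is slightly more powerful. The gap is an assumption throughout. The planned logistic random effects model was only approximated, on the scale of clinic proportions. The change is worth making before the data are seen, because it is cheap and avoids a later choice between two analyses.

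**What to change.** In Sequence generation, describe the allocation as randomisation stratified by municipality, with two clinics per arm in each. If the present sentence means that no further stratification was used within a municipality, say so.

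In the sections on primary and secondary outcomes and on additional analyses, include municipality as a fixed effect in the primary and secondary effect models, whatever the observed balance. State a small-sample reference distribution with 5 between-clinic degrees of freedom (8 clinics less intercept, arm and municipality). Say whether the estimate called raw also carries the term.

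The cost is a few lines of text and one of six between-clinic degrees of freedom. If the municipalities do not differ, power in a clinic-level test falls by about 3 points (75.5% to 72.3%).
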